#### Secondary quantitative analysis

Within group analysis are planned for the patient reported outcomes. These include repeated responses from the BRFSS [42], SF8 [43], and SSI [44] scales that employed Likert type response formats, with the exception of SSI question 7 (Yes or No: Are you currently married or living with a partner?). Individual items from these three scales will be tabulated and summarized at each administration of the questionnaire. The outcome at each time point for a given subject on a given scale will be the sum of the scores of the items from that scale (excluding SSI question 7). Analyzing the total scale score as opposed to the individual items will hedge against the possibility of a large number of ties between the baseline and follow up questionnaires.

During CES-D-R 10 [46] administration, LINKS participants respond to a list of ways they may have felt or behaved during the past week. A total score for the SHS [45] can be obtained by adding the values of the responses to each item, yielding a score from 6 to 48. The physical activity question asks how many days in the past week LINKS participants have done a total of 30 min or more of physical activity which was enough to raise their breathing rate. Responses from each survey administration will be tabulated. For each of these outcomes, the paired responses between (1) baseline and 3 months follow up and (2) baseline and 6 months follow up will be modelled using GEE or GLMM.

#### Qualitative analysis

NVivo Software will be used to analyze open ended questions from the CHW follow up visits. We will combine deductive analysis using a social support framework to identify, describe and compare CHW social support as informational, appraisal, tangible, or emotional. In addition, we will utilize a narrative analysis to compile participant stories that will exemplify the role of CHW social support for participants’ complex experiences and challenging social and economic conditions.

#### Sample size

Based on projected primary care patients in the clinics, we expect a minimum of 28,000 eligible for recruitment based on a more restrictive final eligibility criterion: e.g. require more than one indicator of a pre-chronic disease state or chronic disease risk factor. We anticipate needing less than 5% of eligible referrals to reach targeted program participation, with a pool of over 25,000 patients system-wide to serve as potential controls.

It was estimated that 250 participants in the LINKS intervention would provide 90% power to detect a between group difference of 0.3 standardized units using a 4:1 allocation of controls to LINKS participants at a two-sided α = 0.05/8 significance level (Bonferroni corrected for multiple testing), assuming 10% loss to follow-up in the intervention arm.

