#### Primary quantitative outcomes

The primary outcome variables will be extracted from laboratory reports and vitals. They include glycosylated hemoglobin (HbA1c), body mass index (BMI) derived from current weight and height, blood pressure (based on repeated systolic and diastolic reports) and blood lipid profile (e.g. LDL-C, TC, TC/HDL and triglycerides). Data will be abstracted from raw levels when available, with occurrences of chronic disease risk factors identified as consistent with nationwide studies, such as the CDCs’ National Health and Nutrition Examination Survey (NHANES) [40] and the National Diabetes Prevention Program [41].

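### Bonferroni at 0.05/8 is the only multiplicity rule stated for the primary outcomes; Holm's step-down over the same eight tests gives the same error control with equal or greater power

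*Protocol article*

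**What the plan says.** The Sample size section fixes the level for each test as "0.05/8 significance level (Bonferroni corrected for multiple testing"), two-sided. It does not say which eight tests the divisor counts. The planning aim is "90% power to detect a between group difference of 0.3 standardized units". The target behind that aim is 250 people in the intervention group, with four controls for each of them and a 10% allowance for loss among the former.

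The section on primary quantitative outcomes lists HbA1c, BMI, blood pressure (systolic and diastolic) and a "blood lipid profile (e.g. LDL-C, TC, TC/HDL and triglycerides"). The same section describes abstraction from raw levels where available, "with occurrences of chronic disease risk factors identified as consistent with nationwide studies".

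The section on primary quantitative analysis sets the analysis at 6 to 12 months after program entry and names mixed models or generalized estimating equations. It names no multiplicity procedure. Table 2 lists health-record data at 3 months, 6 months and 1 year, under four headings: HbA1c, BMI, blood pressure and lipids.

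**The concern.** Where several primary outcomes are each tested for a claim, a fixed 0.05/8 for every test is the simplest valid rule but not the most efficient one. One intervention aimed at cardiometabolic risk could plausibly move several of these measures together. In that situation the later, smaller effects are held to a stricter level than familywise control requires. The loss is power on individual endpoints, with no gain in error control.

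A second, smaller matter is tied to the first. Any step-down procedure needs a closed list of hypotheses, and the article gives the number eight without the list.

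**Working it through.** **Inputs.** From the Sample size section: α = 0.05/8 = 0.00625 two-sided, power 0.90, difference 0.3 SD, four controls per participant, 10% loss in the intervention arm, stated N = 250. Assumed, because the article does not give them: the number of real effects among the eight (1, 4 or 8), a common correlation between test statistics (0, 0.3 or 0.6), and 0.2 SD as a smaller effect for sensitivity.

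**Step 1: reproduce the stated size.**
- n(intervention) = (z₁₋α/₂ + z₁₋β)² × (1 + 1/4) / d² = (2.734 + 1.282)² × 1.25 / 0.09 = 224 evaluable.
- Allowing for 10% loss: 224 / 0.9 = 249, against the stated 250.
- Check: 250 × 0.9 = 225, and 225 × 4 = 900. SE = √(1/225 + 1/900) = 0.0745. The standardized effect is 0.3 / 0.0745 = 4.025. Power = Φ(4.025 − 2.734) = 0.902, or 0.900 with the t distribution.
- If loss falls only on the intervention arm (225 against 1,000), power is 0.908 by the normal approximation.

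The plan's figure is confirmed at its stated level.

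**Step 2: the two procedures.**
- Bonferroni rejects hypothesis i if pᵢ ≤ 0.05/8.
- Holm orders the p-values and compares the smallest with 0.05/8, the next with 0.05/7, and so on to 0.05/1, stopping at the first failure.

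Every Holm threshold is at least 0.05/8, so any p-value at or below 0.05/8 is rejected by both. The first step is identical, so the chance of at least one rejection, and hence the planned N, does not change. Holm controls the familywise error whatever the dependence among tests.

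**Step 3: power per real effect.** Eight two-sided z-tests, 225 against 900, 200,000 simulated trials per scenario. Ranges run over the three correlations.

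| True difference | Real effects | Bonferroni | Holm |
|---|---|---|---|
| 0.3 SD | 1 of 8 | 0.90 | 0.90 |
| 0.3 SD | 4 of 8 | 0.90 | 0.92 |
| 0.3 SD | 8 of 8 | 0.90 | 0.96–0.98 |
| 0.2 SD | 1 of 8 | 0.48 | 0.48 |
| 0.2 SD | 4 of 8 | 0.48 | 0.51 |
| 0.2 SD | 8 of 8 | 0.48 | 0.58 |

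The simulated familywise error was at most 0.05 for both procedures in every scenario that contained true null hypotheses.

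**Step 4: what the divisor could count.**
- Reading A: HbA1c, BMI, systolic, diastolic, LDL-C, TC, TC/HDL and triglycerides, one test each: 4 + 4 = 8.
- Reading B: the four headings of Table 2 at two times, 6 and 12 months: 4 × 2 = 8.

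Under Reading A the 6 to 12 month window need not add tests, since a mixed model or estimating-equation model can give one contrast per measure across it. Both readings are compatible with the text.

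**The case against.** Bonferroni at 0.05/8 is valid for eight tests, the sample size is right at that level, and Holm changes neither N nor the chance of a first rejection. All of this stands, so the point concerns efficiency only.

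Bonferroni appears only as the planning level. The analysis section names no procedure, so planning at 0.05/8 and then testing with Holm is already compatible with the article. This also stands: a reader might infer that the final tests will use plain Bonferroni, but the article does not say so. It remains the only multiplicity rule stated, and a reader applying the article as written would have nothing else to use.

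The largest gains need all eight effects to be real at the same size. With one real effect the gain is practically nil. This is correct, and the table shows it.

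Two stronger readings are tempting. The first is that eight can only mean eight continuous measures at one time; Reading B shows otherwise. The second is that the lipid examples, the risk-factor occurrences and the 6 to 12 month window mean that more than eight tests will be run. If, say, 16 tests were each run at 0.05/8, the familywise bound would be 16 × 0.00625 = 0.10, or 1 − (1 − 0.00625)¹⁶ = 0.095 if independent. But no section states 16 tests, and the sentence on occurrences describes how data are abstracted and risk factors identified, not a second set of primary tests. An open list is also a detail that an analysis plan, not shown here, would normally settle.

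**Conclusion.** The point holds as a low-cost improvement in method. For the same eight tests and the same familywise 0.05, Holm is never worse than Bonferroni. At 0.3 SD it adds from almost nothing (one real effect) through about 2 percentage points (four) to about 5 to 7 (all eight). At 0.2 SD the gains are about 0, 3 and 10 points. These figures assume 225 against 900 evaluable, equal effect sizes among the real effects, and a common correlation between 0 and 0.6.

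The article does not contain an error in its significance level or sample size, and it does not show an inflated familywise error. Running more than eight tests at 0.05/8 would take the bound above 5%, but the article does not say that this will happen.

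**What to change.** State in the analysis plan that the eight primary contrasts will be tested with Holm's step-down procedure at a familywise two-sided 0.05. Keep 0.05/8 in the sample-size section as the planning level; N stays at 250.

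In the same place, name the eight contrasts: the measure, its scale (raw level or risk-factor occurrence), and either the time point or the single model contrast over 6 to 12 months. The divisor then matches a closed list. Which eight they are is for the investigators to decide.

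The cost is a sentence for the procedure and a short list. The one real drawback is that simultaneous confidence intervals matching Holm are less simple. Report Bonferroni-level intervals (99.375%, that is 1 − 0.05/8) beside the Holm-adjusted p-values, and note that an interval may include zero for an endpoint that Holm rejects at a later step.

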### Ethics and data sharing approvals

The University of Arizona Institutional Review Board (IRB) approved all stages of our research (IRB Protocol Number 1612044741R001). Due to the iterative development process of LINKS we frequently submitted amendments to ensure that our consent form (see Additional file 2), questionnaire, procedures, and protocols were functional in the three community settings. The majority of modifications to the IRB process were based on CHW feedback. One participating clinic has an institutional review board that also approved LINKS. CHWs obtained written consent from all LINKS participants.

The largest of our partner clinics oversees the EHR system for the other two, smaller partner clinics. In order to access EHR data, we signed an agreement with each clinic. Information technology specialists at the larger clinic oversaw EHR data extraction for all clinics. Using Box Health, a Health Insurance Portability and Accountability Act (HIPAA) compliant cloud storage and file sharing system, we established a secure data transfer protocol with the larger clinic.

## Discussion

The LINKS intervention has practical implications for the development of CCL models. With a focus on providing a continuum of care that extends beyond services offered within clinical settings, LINKS CHWs connect participants to health-specific services and social determinants of health such as housing and transportation. CHWs in community settings have a crucial role to play in CCLS, particularly in identifying existing resources and ensuring that their clients have successfully accessed the referred services [27]. Importantly, CHWs in community settings have the capacity and flexibility to develop additional resources by informing their organizations of client needs or cultivating partnerships between community organizations in order to leverage their efforts [55]. Further, in fulfilling the core function of individual and community capacity building, as defined by the CHW Core Consensus Project [27], CHWs in community settings can help groups organize around specific conditions conducive to health that may or may not be a part of the traditional health sectors [56]. LINKs seeks to investigate how a CHW-led CCL model capitalizes on the strengths of CHWs in both the clinical and community environments.

The LINKS study has strengths and limitations, some in parallel to other health promotion research studies. A limitation in the inference of the intervention solely leading to participant changes is from the lack of randomization to comparison conditions. However, the primary outcomes will use a larger pool of comparators than would be feasible from a randomized clinical trial, and we planned our models to carefully adjust for potential confounding. Such designs that balance generalizability in community-based research with relatively strong casual inferences have been increasingly called for in public health and health promotion research [57–59]. Also, our quantitative evaluation approaches balance the utilization of research collected data and available unobtrusive data with integrated qualitative components.

Our experience in developing and implementing the intervention has some parallels to that of our Prevention Research Center (PRC) network peers. This network of centers is one of the major U.S. governmental efforts to test scalable health promotion research. PRC awardees investigate how communities avoid or counter the risks for chronic disease by identifying gaps in research, developing innovative solutions, and improving public health. In a survey of PRCs with CCL models, researchers across the network identified opportunities and barriers to CCL implementation [60]. It was found that CCLs often require public health stakeholders to communicate in new ways to successfully refer participants to the program and that it takes time to establish efficient collaborations. LINKS intervention partners in all three communities faced challenges in the process of creating a system of participant identification, referral, and linkage. For example, clinical partners had established protocols regarding referral processes which do not necessarily facilitate CHW communication across different organizations.

Practice-based public health research such as LINKS may provide future researchers and public health professionals with examples of adaptable and effective CCL models [61]. However, clinic staff’s unfamiliarity with CHWs’ roles and CHWs’ lack of access to patient healthcare information are some impediments to CHW-led CCLs. While our clinic-based CHWs have EHR access, our community-based CHWs are limited to the data they gather from LINKS participants. After participant consent, the community-based CHWs are able to discuss medical information using the REDCap messenger. This model may leave an incomplete picture of patients’ overall health relative to the information that is accessible directly within the primary care systems. In the future, giving community-based CHWs access to patient medical records would create opportunities for more complete, holistic understanding and documentation of both medical and social determinant needs.

Similar to many CHW interventions, LINKS overwhelmingly recruited women to the study. As all the LINKS CHWs are women, this may have further deterred men from participating. Additionally, our partners observed that Latino men in their community are more focused on economic issues related to being the head of their households than on their health. In contrast, Latina women in their community demonstrate more concern for healthcare issues and as a result are more interested in participating in interventions like LINKS.

Also of note, LINKS communities had varying medical and social determinant services available. CHWs in an urban site could more easily resolve some issues versus in a rural site where there were more limited resources. Conversely, making interconnections to existing resources may be less complicated in rural sites. This could prevent some CHWs from addressing all identified social determinants needs; however, this heterogeneity in community contexts leads to greater generalization of this study’s findings. Finally, EHR data can be challenging to analyze due to inconsistent documentation and lack of some detail [32].

As a participatory research project, the university-based team will disseminate LINKS findings and lessons learned with equal agency of CAB members. Each CAB partner will share the information locally. Community partners will be included in writing up LINKS findings to scientific audiences and media. Both CAB and university-based team members will also continue to present findings at local and national conferences.

In summary, this paper presents the protocol for a prospective matched observational study designed to evaluate the impact of LINKS, a CHW-led CCL model to address chronic disease prevention and management and emotional well-being among Latinos living in three U.S./Mexico border communities. By providing a detailed account of our methodology, this model can be replicated in research and practice.

## Abbreviations

AzCHOW: Arizona Community Health Worker Outreach Association
AzPRC: Arizona Prevention Research Center
BRFSS: Behavioral Risk Factor Surveillance System
CCL: Community Clinical Linkage
CDC: Centers for Disease Control and Prevention
CES-D-R 10: Center for Epidemiologic Studies Depression Scale
CHD: County Health Department
CHW: Community Health Worker
EHR: Electronic Health Record
HIPAA: Health Insurance Portability and Accountability Act
NHANES: National Health and Nutrition Examination Survey
PRC: Prevention Research Center
REDCap: Research Electronic Data Capture
SF8: Short Form 8 Health Survey
SHS: State Hope Scale
SSI: Social Support Inventory
